### Sample size and power

While primary analysis will be adjusted for prognostic factors for weight loss, sample size was determined using an equal variance t-test. Preliminary data identified a 1.4 kg loss for Lifestyle alone and 2.7 kg loss for Lifestyle + Stress interventions, with standard deviations of 2.1 and 4.0 kg, respectively, yielding a Cohen’s d of 0.44 [24]. As these measures were taken at 3 months, and the current study is assessing 6-month weight loss, larger effects are likely; however, to reduce the likelihood of using an effect size which is too large [29], the study has been powered for a Cohen’s d of 0.35. This effect comes from assuming the above with both groups having a 4 kg standard deviation. Thus, with 85% power and a Type 1 error rate of 0.05, 148 participants are needed per group for a total of 296 participants. To allow for 10% attrition without loss of power, 340 participants (170 per group) will be enrolled and randomized.

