### Recruiting and screening eligible participants

Participants will be recruited from the Tampa Bay area through flyers, word of mouth, and small media (e.g., websites, clinical trials advertisements) using culturally appropriate recruitment materials designed to engage Black women. Established relationships between Moffitt Cancer Center and the Tampa Bay Community Cancer Network will also be leveraged to aid in the recruitment of community volunteers for this research study. Recruitment campaigns will be conducted across Years 2-5 of the project to enroll approximately 85 participants per each of four waves, allowing for delivery of at least four treatment groups per cohort (two BWL-Stress and two BWL-Alone groups) with approximately 21 participants per group. Based on a conservative estimate of a 35% recruitment yield obtained from our preliminary research [24, 30], we anticipate pre-screening approximately 970 individuals (~ 323 per year) to enroll 340 participants over four waves. Method of recruitment will be documented.

Interested individuals will initially be screened by telephone by research staff. Based on preliminary eligibility, individuals will be scheduled for a baseline visit to confirm eligibility and complete the informed consent process. Eligible participants will complete all baseline assessments prior to randomization. The random allocation sequence will be generated with computer-generated random numbers.

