### Statistical analyses

For the primary aim which compares BWL-Stress and BWL-Alone on 6-month weight loss outcomes, weight change (baseline weight subtracted from 6-month weight), will be tested using linear models and adjusted for known prognostic measures for weight loss such as age [50] and baseline weight. Model diagnostics, such as assessing normality of residuals and homoskedasticity, will be performed. If any assumption is violated, appropriate transformations (e.g., log) or analyses (e.g., quantile regression) will be performed. Follow-up analyses will be conducted to examine weight loss at month 12.

The secondary aim examines change in perceived, self-reported psychological stress, and will specifically examine changes in PSS-10 and STRAIN scores and cortisol by intervention group at month 6. Similar to Aim 1, change scores will be created and treated as continuous, and adjusted linear models and baseline outcome measure will be performed with appropriate diagnostics for model assumptions. Stress will also be examined at month 12 using data from the PSS-10.

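### The primary weight model names no term for enrolment wave, although both arms are planned within each of four waves; the likely cost is a slightly wide interval, and a wave term should come with a treatment-group term

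*Protocol article*

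**What the plan says.** Under Recruiting and screening eligible participants, the protocol article describes recruitment over Years 2 to 5, aiming to "enroll approximately 85 participants per each of four waves, allowing for delivery of at least four treatment groups per cohort". The planned layout is "at least four treatment groups per cohort (two BWL-Stress and two BWL-Alone groups) with approximately 21 participants per group". Both arms therefore run inside every wave, so wave is crossed with arm, while treatment groups are nested within arm and wave. On allocation the same section says only: "The random allocation sequence will be generated with computer-generated random numbers". Restriction by wave is neither stated nor excluded.

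Under Statistical analyses, 6-month weight change "will be tested using linear models and adjusted for known prognostic measures for weight loss such as age [50] and baseline weight". The secondary stress outcomes follow the same pattern, with adjusted linear models and the baseline value of the outcome. Neither wave nor treatment group is mentioned as a model term.

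Under Sample size and power, "sample size was determined using an equal variance t-test", and "the study has been powered for a Cohen’s d of 0.35". That calculation treats women as independent.

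**The concern.** Wave is part of how the trial is built: women are enrolled, allocated and grouped by wave. The adjustment set is described as prognostic measures for weight loss, and both examples are participant characteristics. A model built from that sentence as it stands would leave wave out.

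When the arms are close to balanced within waves, differences between waves cancel from the arm contrast. A model without wave still counts those differences as residual noise. The reported standard error is then larger than the contrast's actual variability from this source, so the interval is somewhat wide and the test somewhat conservative. What is at stake is precision and a little power for the primary comparison. The treatment estimate is not biased.

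**Working it through.** **Inputs from the protocol article.** Four waves of about 85; two groups of about 21 per arm per wave, so 4 × 2 × 2 = 16 groups if the minimum is run; SD 4 kg in each arm; Cohen's d 0.35; 148 evaluable women per arm; 85% power; type 1 error 0.05.

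**Assumed, because the article gives no figure.** The share of variance in 6-month change due to wave (2%, 5%, 10%) and the correlation within treatment groups (0.02, 0.05).

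**Step 1, the plan's own figure.** A two-sided equal-variance t-test with d = 0.35 and 85% power needs 147.6 per arm, so 148. The stated number reproduces; power at 148 is 85.1%.

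**Step 2, standard error without wave.** SE = 4 × √(2/148) = 0.465 kg, so the 95% half-width is 1.96 × 0.465 = 0.911 kg.

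**Step 3, effect of the wave term.** With arms balanced within waves and total SD held at 4 kg, a wave share r reduces the residual variance by the factor (1 − r). The excess in the standard error without wave is 1/√(1 − r) − 1. Power uses the noncentral t distribution with d/√(1 − r). It is shown for the stated d of 0.35 and for 1.3 kg/4 kg = 0.325, the ratio given by the pilot difference (2.7 − 1.4 = 1.3 kg) and the 4 kg SD.

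| Wave share r | SE excess without wave | Half-width with wave (kg) | Power, d = 0.35 | Power, d = 0.325 |
|---|---|---|---|---|
| 0 | 0% | 0.911 | 85.1% | 79.6% |
| 2% | 1.0% | 0.902 | 85.8% | 80.4% |
| 5% | 2.6% | 0.888 | 86.8% | 81.6% |
| 10% | 5.4% | 0.865 | 88.6% | 83.6% |

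The gain is 0.7 to 2.0 power points for shares of 2% to 5%, and 3.5 to 4.0 points at 10%.

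**Step 4, simulation with a wave effect only.** The layout was 4 waves × 2 arms × 2 groups of 18, 288 women, 4,000 runs per setting. At r = 2% the mean model SE was 0.469 without wave and 0.466 with it. At r = 5% it was 0.468 and 0.459. The ratio at 5%, 0.468/0.459 = 1.02, is slightly below the formula because only four waves are drawn. Type I error without wave was about 4.6% in both settings: valid and slightly conservative.

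**Step 5, simulation with correlation inside treatment groups as well.**

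| Wave share | Within-group correlation | True SD of contrast | Model SE, no wave | Model SE, wave | Type I error, no wave | Type I error, wave |
|---|---|---|---|---|---|---|
| 2% | 0.02 | 0.542 | 0.470 | 0.465 | 9.0% | 9.5% |
| 2% | 0.05 | 0.646 | 0.469 | 0.463 | 15.7% | 16.3% |

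Here the participant-level interval is too narrow overall, and a wave term alone narrows it slightly further.

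**The case against.** The best counter-argument is that this is an omission and not an error. The covariate list gives examples and is not closed, and a full list is commonly left to an analysis plan, which is not shown. If wave does predict weight change, it could itself be called prognostic and so fall within the list. All of this stands to the extent that wave is unmentioned, not excluded. What remains is that the article does describe its primary model and the kind of covariate it adjusts for, and a design factor set out in its own recruitment section is not among them.

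The size is also small and rests wholly on assumed wave shares. That stands too.

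A reader might infer more than the article supports:

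- **Delivery differs between waves because of COVID-19.** The section on changes due to COVID-19 says that the proposed in-person intervention has been adapted to Zoom. It does not say that some waves were in person and others online, so it is no evidence of a between-wave difference.
- **Omitting wave inflates the standard error by 13% to 31%.** Figures of that size arise only if a random effect for treatment group is fitted and wave is still left out, so that wave variance is counted as group variance. The planned linear model contains no such effect.
- **Allocation is faulty unless it is in permuted blocks within wave.** The allocation sentence settles neither restricted nor unrestricted randomisation, and an article commonly leaves that detail to the full protocol. The group numbers are approximate and minimum figures, so an uneven split would not contradict them.
- **The interval will be too wide overall.** This is true only for the wave effect taken alone. Any appreciable correlation within treatment groups pushes the other way, and by more.

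**Conclusion.** The point holds as a modest one. As described, the primary model would leave between-wave variance in the residual, although both arms run in every wave. For assumed wave shares of 2% to 5%, the standard error is about 1.0% to 2.6% too wide (5.4% at 10%), and the cost is about 1 to 2 power points (up to 4). This takes the arms as roughly balanced within waves and the total SD as 4 kg. There is no bias, and type I error is not inflated by the omission itself.

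The larger matter in the same design is that women are treated in groups nested within arm. With a within-group correlation of 0.02, type I error is about 9% with or without wave. A wave term is therefore worth adding for precision but cannot by itself give an interval of the right width.

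**What to change.** Under Statistical analyses, name wave as a four-level fixed factor, together with age and baseline weight, in the primary model and in the secondary linear models at months 6 and 12. In the same change, add a term for treatment group (for example a random effect), so that the wave term accompanies the allowance for clustering and does not stand in for it.

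The cost is a sentence or two of text. No extra participants, visits or data are needed, since wave is known for every woman. In the participant-level model, wave uses three degrees of freedom out of about 290. In a model based on 16 treatment groups, the same three come out of 16 − 2 = 14, leaving 11. The term still earns its place there, because otherwise wave variance is counted as group variance. For waves already randomised, only the model specification changes.

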**Methods:**

Adult Black females with obesity (*n* = 340) will be randomized to either a culturally targeted stress management-enhanced BWL intervention (BWL-Stress) or the same BWL intervention alone (BWL-alone). The primary outcome is weight change at month 6. Secondary outcomes will include changes in stress measures (e.g., perceived stress, cortisol), energy intake, and physical activity at month 6. We will also assess process measures (e.g., treatment adherence, treatment burden). Each outcome will also be evaluated at month 12 to assess longer-term effects of the intervention.

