### Aims and hypotheses

This study examines whether a culturally-targeted, stress management-enhanced BWL intervention (BWL-Stress) is effective in reducing weight compared to a standard BWL intervention (BWL-Alone) among adult Black females with obesity and elevated stress levels. The primary aim is to conduct a randomized controlled trial to determine the effects of BWL-Stress on body weight compared to BWL-Alone among adult Black females with obesity and elevated perceived stress. Black women with co-existing obesity and elevated stress as measured by a validated survey will be randomized to BWL-Stress or BWL-Alone. We hypothesize that BWL-Stress will lead to greater weight loss at 6 months than BWL-Alone. The second aim is to evaluate the effects of BWL-Stress on multidimensional stress as measured by a validated survey instrument and a stress biomarker. Perceived psychological stress will be measured by the Perceived Stress Scale (PSS-10) [27] and the Stress and Adversity Inventory (STRAIN) [28], and salivary cortisol (assessing the cortisol awakening response) will be collected as an objective measure of stress at baseline and multiple follow-up time points to be able to compare changes by intervention group over time. We hypothesize that BWL-Stress will lead to greater reduction in perceived stress and more improvement in cortisol level at 6 months than BWL-Alone. The third aim is to determine whether the relationship between BWL-Stress and weight change is mediated by perceived stress, energy intake, and/or physical activity. A multiple mediation model will be used to determine if perceived stress level, energy intake, and/or energy expenditure explain observed relationships between the stress management-augmented intervention and weight change. We hypothesize that the relationship between BWL-Stress and 6-month weight change will be partially mediated by PSS-10 score, energy intake, and physical activity.

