#### Secondary outcomes

##### Stress

Participants’ perception of psychological stress will be assessed using the PSS-10 and STRAIN. The PSS-10 measures the degree to which an individual perceives life events to be stressful. Sample items include: “In the past month, how often have you felt that you could not cope with all the things that you had to do?” and “How often have you felt that you were unable to control the important things in your life?” Responses are on a 5-point Likert sale (0 = never to 4 = very often). Four items (e.g., “felt confident about ability to handle personal problems”; “I felt things were going my way”) are positively worded and will be reverse coded for analysis. Higher total scores correspond to greater perceived stress. The PSS-10 has been validated in diverse populations and demonstrated to have good internal consistency (α = 0.77) in a previous study conducted by our group among a similar population [46]. STRAIN is an instrument that measures cumulative exposure to life stress, with questions on acute life events, chronic difficulties, and early life stressors [28]. STRAIN contains approximately 220 total questions, with automated omission of questions that are inappropriate for the respondent’s demographic characteristics. STRAIN is structured with close-ended core questions about 55 distinct stressors related to major life domains (e.g., health, education, work, finances, housing, living conditions, intimate relationships, friendships, crime, etc.) and follow-up questions regarding the severity, frequency, timing, and duration of each stressor. A set of 20 lifetime stressor scores will be created based on STRAIN responses. Objective stress will be measured by salivary cortisol via SalivaBio Oral Swab (Salimetrics, LLC, Carlsbad, CA, USA) at baseline and 6-months to correspond with the primary study outcome of weight loss at 6 months. Participants will be provided with a Salimetrics Swab Saliva Collection Kit that includes 9 swabs and tubes. Participants will be asked to collect saliva upon waking and at 30- and 60-min after waking for 3 consecutive days. Participants will be asked to store the samples in their home freezer until they return the samples to our research team after completion at each time point.

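### STRAIN is defined as cumulative lifetime stress exposure, yet its 6-month change score is used to test a reduction in perceived stress

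*Protocol article*

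**What the plan says.** The Stress subsection under Secondary outcomes describes the instrument: "STRAIN is an instrument that measures cumulative exposure to life stress, with questions on acute life events, chronic difficulties, and early life stressors". It adds that "A set of 20 lifetime stressor scores will be created based on STRAIN responses". Core items on 55 stressors are supplemented by "follow-up questions regarding the severity, frequency, timing, and duration of each stressor". No score limited to a recent period, or to the time since baseline, is described.

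Aims and hypotheses and the Stress subsection nevertheless both name STRAIN alongside the PSS-10 as a measure of perceived psychological stress. Aim 2 hypothesises that perceived stress will fall more, and cortisol improve more, with BWL-Stress at 6 months. Statistical analyses puts this into practice: the secondary aim "will specifically examine changes in PSS-10 and STRAIN scores and cortisol by intervention group at month 6", using continuous change scores in adjusted linear models. At month 12, that section examines stress with the PSS-10 only.

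On cortisol, Aims and hypotheses says it "will be collected as an objective measure of stress at baseline and multiple follow-up time points". The Stress subsection has it measured "at baseline and 6-months to correspond with the primary study outcome of weight loss at 6 months". The Abstract lists cortisol among the secondary outcomes and then says: "Each outcome will also be evaluated at month 12 to assess longer-term effects of the intervention".

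**The concern.** A change score tests a reduction only if the quantity measured can go down. The PSS-10 can: its sample item asks about the past month, so a calmer month gives a lower score. A lifetime exposure score is a different kind of quantity. Past events stay in it, and stressors from early life are fixed in women aged 21 to 75.

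If the plan is followed as written, one of the three named Aim 2 outcomes has no clear reading. No change, or an increase, is what accumulation predicts even if the intervention works well on perceived stress, yet it would be reported beside the PSS-10 as evidence that stress was not reduced. A fall could be credited to the intervention when it shows only that past events were rated or recalled differently.

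**Working it through.** The plan states no effect size, power or target for STRAIN, so there is no figure to reproduce. The sample-size calculation concerns weight and does not bear on this point. The check is one of definitions.

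**Step 1: what the score is.** Let E0 be true cumulative exposure at baseline, E6 the same at month 6, and N the exposure added in between.

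E6 = E0 + N, with N ≥ 0, so E6 − E0 = N ≥ 0.

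The change score therefore measures N, new exposure over six months, plus any change in how earlier stressors are reported or rated.

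**Step 2: what the hypothesis needs.** Aim 2 needs a quantity that falls, and falls more in BWL-Stress. N cannot be negative.

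**Step 3: what each observed result would mean.**
- A fall in the score: earlier stressors were re-appraised or recalled differently.
- No change or a rise: compatible with ordinary accumulation, whatever happened to perceived stress.
- A difference between arms: at most, a difference in new exposure, or in reporting.

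**Step 4: can the arms differ at all?** Yes. As an illustration, assume that new stressors follow a Poisson distribution with a mean of 0.25 to 2 per participant over six months, with 170 per arm and no recall error. These accrual rates are assumptions; the documents give none. The change is compared between arms at the two-sided 5% level. The lowest simulated change is 0 and the mean change is positive in both arms throughout. Rejection rates by ratio of new stressors, BWL-Stress to BWL-Alone:

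| Mean new stressors, BWL-Alone | Ratio 1.0 | Ratio 0.8 | Ratio 0.5 |
|---|---|---|---|
| 0.25 | 5.4% | 15.9% | 77.7% |
| 0.5 | 5.4% | 28.6% | 96.8% |
| 1 | 4.9% | 50.9% | 100% |
| 2 | 5.6% | 79.7% | 100% |

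If the intervention leaves the number of new stressors unchanged, a significant result appears only at about the type I error rate, however much perceived stress improves. If it does alter that number, the analysis can detect it, but what it detects is exposure.

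**Step 5: cortisol time points.** The Stress subsection fixes baseline and month 6, and Statistical analyses limits month-12 stress to the PSS-10. These two agree. The plural follow-up time points in the Aims and the month-12 sentence in the Abstract do not match them.

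**The case against.** The strongest reply is that the score is not a pure count. The follow-up items include severity. If severity is self-rated, it is an appraisal that can move down, and BWL-Stress works on appraisal (session 12 on all-or-nothing thinking, session 16 on restructuring thoughts). The arms might also differ in new difficulties, since sessions 13 to 15 cover money and setting limits. Both points stand. A reader might infer that STRAIN change can show nothing, or that any fall is faulty recall; the documents do not support either, because reported severity can fall and new exposure can differ. What remains is that re-rating past events, or meeting fewer new ones, is not the drop in perceived stress that Aim 2 states, and no re-appraisal score is described.

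A reader might also infer inflated reporting in BWL-Stress alone, because its session 2 teaches women to recognise what triggers their stress. Table 1 does not support a one-sided effect. BWL-Alone covers domestic violence, addictive behaviours and health insurance in sessions 8, 10 and 11, which touch STRAIN life domains, and both arms receive the curriculum's own stress session (session 15). Reporting could shift in either arm.

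Third, a reader might take the 20 scores as 20 tests. The article says that 20 scores are created, not that all are tested. The choice among them may properly be left to the analysis plan. That choice would not cure the mismatch, because all are described as lifetime scores.

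On cortisol, a reader might infer that a month-12 result is firmly promised. It rests on one summary sentence in the Abstract, which the detailed sections override.

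**Conclusion.** The concern holds as a mismatch between construct and hypothesis. The article defines STRAIN as cumulative lifetime exposure, labels it perceived stress, and tests its 6-month change under a hypothesised reduction. The lower bound of zero applies to true cumulative exposure and to stressor counts, not to every reported score. The conclusion rests on the article's own description of the instrument and on there being no time-limited score that it leaves unmentioned.

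The reach is modest. One secondary outcome would be uninterpretable as evidence on Aim 2. The primary outcome is weight, and the stress mediator in Aim 3 is the PSS-10, so neither is affected. Aim 2 retains the PSS-10 and cortisol. The cortisol mismatch is an alignment of wording, not a flaw in the analysis.

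**What to change.** Remove STRAIN change from the Aim 2 stress-reduction outcomes and keep change in PSS-10 and cortisol. Stop describing STRAIN as a measure of perceived stress in Aims and hypotheses and in the Stress subsection. Use baseline STRAIN as a descriptor, or as one pre-specified covariate or moderator; baseline assessments are completed before randomisation, so it is suitable for this.

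Alternatively, if the STRAIN timing items allow it, define a score restricted to stressors since baseline, name it in advance, and report it as stress exposure.

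As a minor edit, make the Abstract and the Aims agree with the detailed sections: cortisol at baseline and month 6 only, and month-12 stress by PSS-10 only.

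The cost is a change of analysis wording and one fewer listed stress outcome. No new data are needed. Under the first option, the follow-up administration of an instrument of roughly 220 questions could be dropped; the since-baseline alternative needs it kept.

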For Aim 3, which examines whether the relationship between the intervention and weight change is mediated by perceived stress, energy intake, and physical activity, we will determine whether the relationship between each intervention condition and weight loss is mediated by perceived stress (as measured by the PSS-10), caloric intake, or physical activity [51]. Each potential mediator will be evaluated independently using a counterfactual approach [52]. As we are interested in multiple mediators which likely are not independent, we will use inverse odds ratio weighting (IOWR) to estimate the natural direct effect of BWL-Stress and BWL-Alone [53, 54]. This method first estimates weights by using logistic regression (to predict the dichotomous exposure variable) containing all mediators and confounders and creates an odds ratio for each participant. Next, the odds ratios (OR) are inverted (f (OR_i_) = OR_i_^− 1^) for each participant to create an IORW weight with standard BWL participants having weight 1. Direct effects of the intervention are estimated using weighted linear regression models including confounders and no mediators using IORW weights. The total effect of the intervention on weight loss is then estimated using an unweighted linear regression with the same confounders as the weighted analysis. The indirect effect is then estimated by subtracting the direct effect from the total effect. Confidence intervals for the effects are created using bootstrap methods. All analyses will be intention-to-treat. Baseline observation carried forward, which conservatively estimates a return to pre-treatment weight, will be used for participants without follow-up outcome measures for the primary outcome of weight. For participants missing data other than the primary outcome, we will perform multiple imputation as appropriate, as complete case analyses are known to be biased.

Missing data will be handled using multiple imputation by chained equations (MICE) with auxiliary variables identified using procedures from Enders [55]. Estimates from different imputed datasets will be combined using Rubin’s rules, and these will be integrated with inverse weighting mediation measures based on Stata code from previous similar work [55]. Multiple imputation is superior to complete case analysis if the missing complete at random assumption is violated. The likelihood of meeting the missing at random assumption will be bolstered with the use of auxiliary variables.

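### Aim 3 sets lost women's weight change to zero but imputes their mediators as missing at random, so unequal dropout would distort the direct/indirect split

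*Protocol article*

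**What the plan says.** The Statistical analyses section gives two missing-data rules. For the primary outcome of weight: "Baseline observation carried forward, which conservatively estimates a return to pre-treatment weight, will be used for participants without follow-up outcome measures". For all other data: "For participants missing data other than the primary outcome, we will perform multiple imputation as appropriate". The imputation uses chained equations, and its assumption is named: "The likelihood of meeting the missing at random assumption will be bolstered with the use of auxiliary variables". The section then ties the imputations to the mediation analysis: "these will be integrated with inverse weighting mediation measures based on Stata code from previous similar work".

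Aims and hypotheses names the outcome and mediators of Aim 3: "the relationship between BWL-Stress and 6-month weight change will be partially mediated by PSS-10 score, energy intake, and physical activity". That outcome is the trial's primary outcome. On estimation: "Direct effects of the intervention are estimated using weighted linear regression models including confounders and no mediators using IORW weights". The total effect comes from an unweighted regression, and the indirect effect is total minus direct. Every analysis is intention-to-treat, so lost women stay in Aim 3.

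The last paragraph of the section opens with a general statement that chained equations will deal with missing data. It does not mention weight, and it does not withdraw the carried-forward rule.

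**The concern.** The two rules assume different things about the same woman. Carrying baseline forward says that she lost no weight. Imputing under missing at random says that her stress, intake and activity are what one would expect of comparable women who stayed.

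The two assumptions meet in two linked steps of one analysis: a logistic model containing the mediators, which produces the weights, and a weighted regression of weight change. The zeros pull each arm's mean weight change towards zero in proportion to its dropout, and the imputed mediators show no matching change. A difference in dropout therefore creates a weight difference that the mediators cannot explain, and this method assigns whatever the mediators do not explain to the direct effect.

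Aim 3 is the basis for what the Discussion hopes to say about mechanism. Its split should not depend on which arm happens to lose more women.

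**Working it through.** **The plan's own figures.** None is given for Aim 3. The sample-size figure in the section that supplies the inputs does reproduce: a two-sided two-sample t-test with d = 0.35, alpha 0.05 and 85% power needs 147.6, that is 148 per group.

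**Inputs from the protocol article**
- Sample size and power: pilot losses of 1.4 and 2.7 kg at 3 months (difference 1.3 kg), planning SD 4 kg, 170 per group, attrition 10% overall.
- Background: a 6-month loss of 4.7 kg among Black women in the Diabetes Prevention Program.

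**Assumptions**
- Dropout by arm of 15% and 5%, in either direction (10% on average).
- Dropout random within arm; mediators imputed by arm.
- True total effect -1.30 kg.
- A control loss of 3.4 kg is 4.7 - 1.3, which places the cited 4.7 kg in the BWL-Stress arm.

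**Formula.** Let d1 and d0 be the dropout shares in BWL-Stress and BWL-Alone, mu0 the mean change in BWL-Alone (negative for a loss), D the true direct effect and I the true indirect effect.
- Weighted BWL-Stress mean: (1 - d1)(mu0 + D)
- BWL-Alone mean: (1 - d0) mu0
- Direct = difference = (1 - d1) D - (d1 - d0) mu0
- Total = (1 - d1)(mu0 + D + I) - (1 - d0) mu0
- Indirect = total - direct = (1 - d1) I

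The term -(d1 - d0) mu0 comes from dropout alone.

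**Equal 10% dropout, half mediated (D = I = -0.65).** Direct = 0.9 x -0.65 = -0.585; indirect = -0.585; total = -1.17. Both effects shrink by 10%, and the proportion mediated stays at 50%.

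**Shift in the direct effect for a 10-point gap**
- Control loss 1.4 kg: 0.10 x 1.4 = 0.14 kg, or 11% of 1.3 kg.
- Control loss 4.7 kg: 0.10 x 4.7 = 0.47 kg, or 36% of 1.3 kg.

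**Proportion mediated when the truth is 50%**

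| Control loss | Dropout Stress / Alone | Direct | Indirect | Mediated |
|---|---|---|---|---|
| 1.4 kg | 5% / 15% | -0.6175 - 0.14 = -0.76 | -0.62 | 45% |
| 1.4 kg | 15% / 5% | -0.5525 + 0.14 = -0.41 | -0.55 | 57% |
| 3.4 kg | 5% / 15% | -0.6175 - 0.34 = -0.96 | -0.62 | 39% |
| 3.4 kg | 15% / 5% | -0.5525 + 0.34 = -0.21 | -0.55 | 72% |

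**Simulation check.** 400,000 women, three mediators explaining 30% of the variance, SD 4 kg, full mediation (true direct 0, indirect -1.30).
- Plan as written, dropout 15% Stress / 5% Alone: direct +0.13 at a control loss of 1.4 kg and +0.47 at 4.7 kg. The formula gives +0.14 and +0.47.
- The same, with the carried-forward zeros used as predictors in the imputation: +0.09 and +0.54. At equal 10% dropout this version gives +0.03 (the full data in that run gave +0.01) and +0.15.
- Weight imputed together with the mediators, all scenarios: direct -0.01 to +0.02, indirect -1.29 to -1.32.

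The last result shows that the two assumptions then agree. It does not show that missing at random is true, because the simulated dropout was built to satisfy it.

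**Scale.** The standard error of the total effect with 170 per group is 4 x sqrt(2/170) = 0.43 kg. The shifts of 0.14 and 0.47 kg are about 0.3 and 1.1 standard errors.

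**The case against.** Four points can be made for the plan.

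1. **Attrition.** The protocol gives only 10% overall. If that loss is equal in both arms and the mediators are imputed by arm, the proportion mediated is unbiased. This stands. A reader might infer that Aim 3 will report differential dropout as a direct effect, but no passage gives dropout by arm. The massage vouchers described for BWL-Stress, and the Background's report of lower attendance by participants of color in an earlier mindfulness arm, make a difference plausible. They do not give its size or direction, and attendance is not dropout.

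2. **Wording.** The general sentence on chained equations, followed by the link to the mediation analysis, could mean that Aim 3 uses imputation throughout and that carried-forward weight belongs to the primary test only. This is a fair reading. However, the carried-forward rule is written for the primary outcome of weight without limit to one aim, and the other rule excludes that outcome from imputation. At the least, the two passages need reconciling.

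3. **Auxiliary variables.** Month-4 data, attendance and self-monitoring could make the imputed mediators reflect a poor early response. That would soften the conflict. It would not remove it, because weight would still be fixed at zero.

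4. **Month 12.** The plan says "Follow-up analyses will be conducted to examine weight loss at month 12". A reader might infer that month-12 weight is imputed while month-6 weight is set to zero, so that the two visits are not comparable. The document does not support this: the section headed Primary outcome: anthropometry covers 12-month weight too, so one rule for both visits is the more natural reading.

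**Conclusion.** The point holds for Aim 3 only. As written, the rules give a lost woman zero weight change beside mediators modelled on women who stayed, and the direct/indirect split is then sensitive to unequal dropout. For an assumed 10-point gap the direct effect shifts by 0.14 to 0.47 kg as the control loss runs from 1.4 to 4.7 kg. The sign follows the arm that loses more: heavier loss in BWL-Stress works against a direct benefit, and heavier loss in BWL-Alone creates one.

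These sizes rest on random dropout within arm and imputation by arm. With equal dropout the split is undistorted, unless the carried-forward zeros enter the imputation model, whose content the article does not settle. At the pilot control loss the error is modest beside sampling error. The primary test is not affected. This is a worthwhile correction to an explanatory third aim.

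**What to change.** State which missing-data rule applies to weight in Aim 3, and use one assumption for outcome and mediators:
- Impute 6-month weight jointly with PSS-10, energy intake and physical activity, with treatment arm and month-4 data in the model.
- Estimate the total, direct and indirect effects on those imputed datasets.
- Keep carried-forward weights out of the imputation model.
- Retain the carried-forward version of Aim 3 as a sensitivity analysis.

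The cost is a few lines of analysis-plan wording and a slightly larger imputation model. The Aim 3 total effect may differ from a carried-forward primary estimate, which needs one explanatory sentence.
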